## Abstract

**Background:**

Work-related stress has become a major challenge for social security and health care systems, employers and employees across Europe. In Sweden, sickness absence particularly due to stress-related disorders has increased excessively in recent years, and the issue of how to improve sustainable return to work in affected employees is high up on the political agenda. The literature on interventions for return to work in patients with common mental disorders is still inconclusive. This randomized controlled trial (RCT) aims to contribute with knowledge about how physicians and rehabilitation coordinators in primary health care can involve the employer in the rehabilitation of patients with stress-related disorders. The objective is to evaluate whether the early involvement of the patient’s employer can reduce the time for return to work compared to treatment as usual. A process study will complete the RCT with information about what prerequisites primary health caregivers need to succeed with this endeavor.

**Methods:**

Twenty-two primary care centers were randomized to either intervention or control group. At the intervention centers, physicians and rehabilitation coordinators underwent training, providing them with both knowledge and practical tools to involve the employer in rehabilitation. At the patient level, employed patients with an ICD-10 F43 diagnosis were eligible for participation (*n*=132). Difference in proportion of patients on full- or part-time sick leave at three, six and 12 months after inclusion will be investigated. Register data, logbooks and interviews with coordinators and physicians at both intervention and control centers will be used for process evaluation.

**Discussion:**

Although the issue of how to tackle work-related stress can be recognized all across Europe, Sweden face an urgent need to curb the disproportional increase of stress-related disorders in the sick-leave statistics. Since physicians are limited by time constraints, the rehabilitation coordinator may be a helpful resource to take this contact. The current study will contribute to knowledge about how this collaboration can be organized to facilitate employer involvement and reduce time to return to work among patients suffering from work related stress.

**Trial registration:**

Registered on 1 November 2016, ClinicalTrials.gov, NCT03022760.

## Background

Work-related stress occurs when the demands of the job exceed a worker’s ability to cope with them. It is the second most frequently reported work-related health problem in Europe; about one fourth of European workers say they experience work-related stress for all or most of their working time [1]. The considerable costs of stress-related disorders can be found at all levels: loss of health and income for the sick listed employee; loss of productivity, high levels of absenteeism and turnover for the employer and strained health care services and social security systems for the society [2, 3]. To prevent stress at work and to increase work capacity in employees with stress-related disorders is a challenge on a national as well as on the European level.

In Sweden, psychiatric diagnoses are the most common cause to sickness absence (SA), among both women and men [4], and the number of new cases of sick-leave periods^1^ in psychiatric diagnoses rose from 16 cases per 1000 employees in 2010, to 28 cases per 1000 employees in 2016 [5]. Tackling these increasing sick-leave rates is high up on the Swedish political agenda. Exhaustion disorder (ED) is a recognized diagnosis in Sweden since 2005, which justifies compensation from the social security system. Adjustment disorders and reactions to severe stress (Table 1) represent about 50 % of sick-leave cases^2^ due to psychiatric disorders [6].

**Table 1 Tab1:** The International Classification of Disease 2010 F43: Reaction to sever stress, and adjustment disorders

F43.0	Acute stress reaction
F43.1	Post-traumatic stress disorder
F43.2	Adjustment disorders
F43.8	Other reactions to severe stress
F43.8A^a^	Exhaustion disorder
F43.9	Reaction to severe stress, unspecified

^a^This diagnosis has been added to the Swedish ICD-10 scheme

Work-related factors such as high job demands, low job control, and low social support, increase the risk for sickness absence (SA) due to common mental disorders (CMD) in general [7], and for the development of burnout symptoms in particular [8]. For most people, a period of sickness absenteeism ends with the patient returning to work. Apart from a number of important variables at the individual level, such as symptom severity and a strong expectation to return to work (RTW), workplace level factors such as a sufficient social support from colleagues and supervisor are important determinants for a successful RTW process in CMD patients [7, 9]. Employees with low work demands and a strong RTW self-efficacy and work ability have also been shown to be more likely to RTW after a period of SA due to a CMD [10].

In the past years, several reviews and meta-analyses have been concluding the evidence from a growing number of studies on both clinical and workplace interventions for RTW in patients with CMD. These studies include a plethora of operationalizations of sickness absenteeism and RTW and are conducted on patients with different mental afflictions- most commonly anxiety and/or depression. To reduce sickness absenteeism and/or enhance RTW for workers with specific diagnoses, we find support for problem solving therapy (PST) for people with adjustment disorders [11]; for cognitive behavioral therapy (CBT) and work-directed measures for workers with depression [12]; and physical activity [13] and work-directed interventions (such as exposure therapy, CBT- and PST- based RTW programs) in patients with anxiety and/or depression [14]. In a systematic review and meta-analysis focusing on tertiary interventions in clinical burnout, the authors conclude that successful interventions incorporate the employer in rehabilitation [15].

When CMD is more broadly defined, scholars have recommended a cohesive and work-focused rehabilitation program, involving several stakeholders [16], as well as work-focused CBT and interventions including a combination of health focused interventions, service coordination interventions and work modification interventions [17].

But there are also recent reviews where no, or very limited, support for work-directed interventions for improving RTW in workers with CMD were found [18–20]. Thus, there are no univocal conclusions to be drawn from these reviews and any effort to improve RTW in workers with CMD must be done with a careful consideration to the specific institutional context where it is taking place.

In Sweden, the average time (median for all diagnoses) to end a sick-leave case is 44 days. However, for patients with adjustments disorders and reaction to severe stress it takes on average 57 days to end a sick-leave case [6]. The effect of employer involvement in stress rehabilitation has been studied in a Swedish context, and beneficial effects on RTW have been shown [21, 22], also over time for younger patients [23]. In a recent study, CMD patients (out of which over 70 % suffered from exhaustion or adjustment disorder) receiving primary health care were randomized to either CBT; an workplace intervention including early contact with the employer and graded exposure to the workplace; or a combination of the two [24]. One year after intervention however, there was no difference in days on sick leave between the three treatment groups. Research on workplace involvement in the rehabilitation of patients with stress-related disorders are thus inconclusive also in a Swedish context.

All registered physicians have the right to issue sickness certificates in Sweden, and the vast majority of sick-leave notes are dispensed by general practitioners (GP) within the primary health care system. To provide sufficient and accurate information in the sickness certificate is a challenging task for physicians [25]. In recent years, the economic incentives for the primary health care to involve the employer in rehabilitation have been reinforced. A new function- the rehabilitation coordinator (RC) - has been introduced in all Swedish county councils to support sick-listed patients during their rehabilitation. The very objective with this function is to facilitate patients’ RTW. The RC should also provide the health care system with knowledge about the social insurance system, and coordinate actions between different stakeholders around the patient [26]. The role of the RC is under development and there is yet little guidance on best practice for this new group of primary care professionals [27]. This opens up a window of opportunity to evaluate methods that can be used by the RC to enhance RTW among this large patient group.

Several agreements have been settled at the national level between the government and the Swedish Association of Local Authorities and Regions (SALAR) in order to enhance best practice in primary health care when rehabilitating CMD patients back to work. However, these attempts have been criticized for being ineffective in combatting increasing sick-leave rates [28].

With this study we intend to contribute to knowledge about how primary health care – through the RC- can involve the employer in the rehabilitation of patients with stress-related disorders.

## Methods/Design

### Aim

The overall aim of this study is to evaluate whether a systematic procedure of cooperation between GPs and RCs which involves the employer can reduce the time for RTW in patients with stress-related disorders during a 12-month follow-up period. An intervention group will be compared to treatment as usual (TAU). The primary hypothesis is that an early contact between caregiver, patient and employer can stimulate the employer to take measures at the workplace that advance patients’ RTW. However, we expect this relationship to depend on various circumstances, both at the patient and the organizational level, such as the patient’s symptom severity and motivation to RTW, and the participant GPs’ and RCs’ possibilities to adhere to the intervention.

The second aim of the study is to investigate the organizational prerequisites for primary health care centers (PHCC) to involve the employer at an early stage of rehabilitation. This will be done by a process evaluation, using interviews and register data at the center level.

### Setting

In Sweden, county councils are responsible for providing primary health care. Caregivers that comply with regional standards have the right to provide primary health care, and for a modest fee of € 10, citizens have the right to seek care among both public and private suppliers, funded by public means. One important task for Swedish GPs is to issue the sickness certificates that serve as a basis for social insurance benefit assessments, required from the 8^th^ day of a sick-leave period. A sick-leave certificate must contain a large amount of detailed information, for example about the patient’s diagnosis; functional impairments and activity limitation (work incapacity). The physician can seek advice on appropriate sick-leave durations for different diagnoses in a national decision support, issued by the National Board of Health and Welfare to enhance equal treatment over regions and caregivers. The work capacity must be reduced by at least 25 % for the employee to qualify to sickness benefits. The first fourteen days of a sick-leave period is covered by the employer (except for a first qualifying day), thereafter the Social Insurance Agency takes over the financial responsibility [29]. After 90 days of sick-leave, the agency decides on the right to further payments by assessing the employee’s work capacity in relation to all other work tasks offered by the employer. Further benefits are only granted if there are no such possibilities. The employee has the right to be off duty to try another job, with another employer. At day 180, the employee’s work capacity is evaluated in relation to the entire labour market, but only if it can be assumed that the patient will not be able to return to his or her ordinary job before day 365, or if there are other reasonable conditions that inhibit evaluation. Sickness benefits can compensate for an income loss corresponding to 25 %, 50 %, 75 % or 100 % of the employee´s working hours.

The study is conducted in the Västra Götaland region of Sweden, a large county council covering almost 20 % of the Swedish population with 200 public and private PHCCs. There are about 800 GPs employed at these PHCCs and almost all centers can offer the services of a RC. However, coordinators depend on earmarked national subsidies, and it is common for the coordinator to either work part time as for example a nurse or psychologist, or to work as a coordinator at two or even three centers.

The study is conducted at the Institute of Stress Medicine, Västra Götaland region, and the Department of Work Science and Sociology, University of Gothenburg. It is part of the New Ways research program at the Section for Epidemiology and Social Medicine, Institute of Medicine, Sahlgrenska Academy, University of Gothenburg.

### The RCT

#### Target group, recruitment and randomization

The target group for the intervention was GPs and RCs at the included PHCCs, and by extension their patients, sick-listed from work due to a stress-related diagnosis. The recruitment of PHCCs took place between January and October 2016. A first request to the PHCCs to participate were communicated by telephone calls, e-mails and personal meetings with PHCC managers throughout the Västra Götaland region. In order to attain diversity in terms of geographical location, public or private ownership, center size, and the socioeconomic conditions of the area, interested centers were checked against regional register data. We also considered the number of patients with a F43 diagnosis at the center during one year (2015), the center’s involvement in other research projects, and the extent of RC resources at the center.

Out of the 30 public and private PHCCs that were invited to participate, 22 accepted; 15 public and seven private centers. Managers accepted the center’s commitment by signing a contract with the researchers. Managers were asked to make sure that the entire staff agreed to the center’s participation in the study before signing the contract. The researchers visited each center to inform the staff about the study prior to commitment. PHCCs were offered economic compensation for recruited patients; € 50 per patient in the control group and € 100 per patient in the intervention group. Also, all centers were offered the one day training program, however they were informed that if allocated to the control group, they would have to wait until all patients were recruited to the study.

Based on similar characteristics in register data, we matched centers in pairs. From each pair, one center was randomly selected to the intervention group and the other one to the control group. The staff of the participant centers were all aware about their allocation in the RCT, blinding was not possible in this study.

Employed patients with a F43 diagnosis as the main diagnosis, getting their sickness certification renewed were eligible for participation. Excluded were patients with post-traumatic stress disorder, F43.1. Patients who did not read or speak Swedish, and patients who have had a sick-leave period of more than 60 subsequent days during the past three years before inclusion were not asked to participate.

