When a GP had identified a patient for inclusion (step one), the RC set up a meeting with the patient. During this meeting, the RCs informed the patient about the study and collected his or her written consent. The patient filled out a questionnaire containing questions on background characteristics, occupation, symptoms, work stressors and private life stressors, work ability, RTW self-efficacy, employer activities, RTW motivation, and general health (see Table 2). The questionnaire took about 30 minutes to fill in. Patients declining participation were asked to fill in their year of birth, gender and occupation. The RC then used the questionnaire to interview the patient for about one hour (step two), scanned the questionnaire to the medical journal, and provided the GP with a summary. In the next step (step three), the RC called the patient´s employer and filled out a form containing questions about the employer’s view on the situation before and after the patient’s sick-leave, and about the employer’s readiness for the patient’s RTW. This form was also scanned to the medical journal, and the GP was provided with a summary. The procedure ended with a meeting between the RC, the GP, the patient and the employer to set up a plan for RTW (step four). After this final step, the RC filled out a checklist about protocol adherence. All forms and questionnaires also served as research data, and were collected by the researchers.

**Table 2 Tab2:** Content of the patient questionnaire

Item	Label	Questions & references
Q 1-8	Background characteristics	-
Q 9-12	Exhaustion disorder	Questions from Glise et al. [32] on self-reported exhaustion (s-UMS)
Q 13-50	Work stressors	Items from the Work Stress Questionnaire (WSQ) [33]; Job Control Questionnaire (JCQ) [34]; the General Nordic Questionnaire for Psychological and Social Factors at Work (QPS Nordic 34+) [35]; and the Copenhagen Psychosocial Questionnaire (COPSOQ II) [36]
Q 51-53	Work ability	Items from the Work Ability Index (WAI) [37]
Q 54	RTW- self efficacy	Questions from Lagerveld et al. 2010 [38] on return to work self-efficacy (RTW-SE)
Q 55-57	Employer activities before sick-leave	Questions from the method Workplace Dialogue for Return to Work [21, 39]
Q 58-60	RTW motivation	Item on RTW motivation in van Oostrom et al. 2010 [40]
Q 61a-n	Life stressors	Questions from Hasselberg et al. 2014 [41]
Q 62-75	Symptoms of anxiety and depression	Items from the Hospital Anxiety and Depression scale (HAD) [42]

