#### Outcome measurements and statistical analyses

The primary outcome of the RCT is RTW. We will analyze the difference between cases and controls in proportion of patients on full- or part-time sick leave at three, six and 12 months after inclusion. We will use data from the Swedish Social Insurance Agency’s Micro Database for Analyzing Social insurance (MiDAS) where all sick-leaves exceeding two weeks are registered. The intention to treat principle will be followed.

The intervention is designed to facilitate for the caregiver to involve the employer in rehabilitation and strengthen the patient’s RTW-SE, but whether these mechanisms are triggered or not will depend on circumstances among patients, employers as well as the caregivers, i.e it will depend on contextual factors [46]. For example, the effect of the intervention on RTW might depend on the patient’s symptom severity, the employer’s readiness for work adaptation, or on the caregivers’ adherence to the protocol. In order to conduct sub-group analysis within the intervention group, a follow-up questionnaire is sent to the patients’ home address by mail at six and 12 months after inclusion. In addition to questions about the rehabilitation process, the questionnaire contains the same items as the baseline measurement. For example we will explore how gender, age, occupation, symptom severity, employer activities and RTW motivation affect RTW.

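### Elapsed sick leave at inclusion varies and may differ between arms, because unblinded staff recruited after center allocation; the stated comparison of proportions does not account for it

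*Protocol article*

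**What the plan says.** All references are to the protocol article.

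- **Entry** (Target group, recruitment and randomization): "Employed patients with a F43 diagnosis as the main diagnosis, getting their sickness certification renewed were eligible for participation". Which renewal is not stated. The Setting section says a certificate is needed from day 8, so a renewal normally falls later than that.
- **Time limit** (same section): "patients who have had a sick-leave period of more than 60 subsequent days during the past three years before inclusion were not asked to participate". Whether the current spell counts is not stated.
- **Recruitment** (same section, and The intervention): centers were matched in pairs and randomized, and staff knew their allocation. Payment was € 100 per recruited patient in intervention centers and € 50 in control centers. Intervention staff were trained in why and how to involve the employer at an early stage; control centers were offered the training only after their recruitment had ended. Control inclusion opened on the first training day in November 2016, while training days for intervention centers ran to September 2017.
- **Outcome** (Outcome measurements and statistical analyses): the arms are compared on the "proportion of patients on full- or part-time sick leave at three, six and 12 months after inclusion", using the MiDAS register.
- **Typical duration** (Background): "for patients with adjustments disorders and reaction to severe stress it takes on average 57 days to end a sick-leave case".

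**The concern.** How long a patient has already been on sick leave is a likely predictor of whether the patient is still on sick leave three months later. Where patients are randomized individually, chance tends to balance such a factor. Here the centers were randomized, and patients were then selected by people who knew the arm and worked under different conditions in each. If one arm tended to enrol at a first renewal and the other at a later one, the proportions on sick leave could differ without any treatment effect, or a real effect could be masked. The comparison as stated is a plain difference in proportions and offers no protection.

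The timing also bears on interpretation. The Aim section says: "The primary hypothesis is that an early contact between caregiver, patient and employer can stimulate the employer to take measures at the workplace". Neither entry nor the employer call has a day limit, so the result cannot show by itself how much earliness contributed.

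**Working it through.** **1. Range of entry days.** A renewal follows a certificate that is needed from day 8. On the literal reading of the exclusion, the latest entry is day 60, which is 60 − 57 = 3 days beyond the typical case in this diagnosis group. If the rule covers only earlier spells, the documents set no upper limit. They give no distribution of entry days, so day 60 is a possible maximum and not a typical value.

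**2. What the outcome times mean in spell days.** Taking three months as 91 days, the first reading falls on spell day 15 + 91 = 106 for a patient who enters on day 15, and on day 59 + 91 = 150 for one who enters on day 59.

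**3. The plan's own yardstick.** With 69 control and 63 intervention patients, a 15-point difference, two-sided 0.05, and the pooled normal approximation for two proportions, power is 74.0 % at a control prevalence of 20 %, 40.5 % near 57.5 % (the minimum) and 75.0 % at 95 %. This agrees with the stated 41 % to 74 %. The point made here does not change that calculation; the 15 points serve only as a scale for step 4.

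**4. How far entry day could move the three-month outcome.** Assumption, not in the documents: spell length is Weibull with median 57 days and shape k. The article calls 57 days an average; it attaches the word median to the 44-day figure for all diagnoses, so reading 57 as a median is an inference.

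S(t) = exp(−ln 2 × (t/57)^k)

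P(still on sick leave 91 days after entry at day t) = S(t + 91) / S(t)

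Worked case, k = 0.5:
- t = 30: exp(−0.6931 × [(121/57)^0.5 − (30/57)^0.5]) = exp(−0.6931 × 0.7315) = 0.602
- t = 40: exp(−0.6931 × [(131/57)^0.5 − (40/57)^0.5]) = exp(−0.6931 × 0.6783) = 0.625

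| Shape k | Entry day 30 | Entry day 40 | Shift for 10 days | Entry day 15 | Entry day 60 |
|---|---|---|---|---|---|
| 0.5 | 60.2 % | 62.5 % | +2.3 points | 55.5 % | 65.9 % |
| 0.7 | 48.1 % | 49.6 % | +1.5 points | 45.0 % | 52.1 % |
| 1.0 | 33.1 % | 33.1 % | 0 | 33.1 % | 33.1 % |
| 1.2 | 24.9 % | 24.0 % | −0.9 points | 26.7 % | 22.5 % |
| 1.5 | 15.3 % | 13.4 % | −1.8 points | 18.9 % | 10.6 % |

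The last two columns contrast two individual patients at opposite ends. They would describe a bias between arms only if every patient in one arm entered on day 15 and every patient in the other on day 60. The 10-day shift is the more reasonable illustration of a difference between arms.

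**The case against.** **The comparison does not test early contact.** A reader might infer this from the open entry rule. The documents do not support it. The Intervention section says that at some control centers usual care included contact between coordinator and employer, normally long into the sick-leave period. In the intervention arm the employer call is the step after the consent meeting and interview. The arms therefore do contrast earlier, systematic contact with later or no contact. Early is undefined in days, but it is not absent. The Aim section also frames the trial more broadly, to "evaluate whether a systematic procedure of cooperation between GPs and RCs which involves the employer can reduce the time for RTW", and that is what is compared.

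**Follow-up from inclusion is ordinary.** This stands. It is the same origin in both arms and is not a fault.

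**Covariates belong in the statistical analysis plan.** Largely right. An article need not list them, and an analysis plan not shown here may already include entry day. The point is therefore an improvement on the comparison as stated, not an error in it. It deserves raising because this recruitment scheme gives a specific reason to expect that entry day might differ.

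**No imbalance has been shown.** Also right. Nothing in the documents says that the arms differ in entry day, or in which direction.

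**Splitting the effect by entry day would answer the timing question.** It would not. Entry day is not randomized, late entrants are selected for longer spells, and power for the main effect is already only 41 % to 74 %.

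**Conclusion.** The point holds as a modest one. Elapsed sick leave at inclusion is free to vary, the recruitment scheme gives a plausible route to imbalance between arms, and the stated comparison does not account for it. Its size cannot be determined from the documents. Under the Weibull assumption with shape 0.5 to 1, a 10-day difference in entry shifts the three-month proportion by about 0 to 2 points, small beside the assumed 15. A shape above 1 reverses the sign, so even the direction is uncertain. The gap of about 10 points between entry on day 15 and on day 60 (65.9 − 55.5 = 10.4 at shape 0.5) is a contrast between extreme patients and should not be quoted as a bias.

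On interpretation, a difference between the arms would support the procedure as a whole (training, four steps and specialist advice) started at certificate renewal, against usual care. It would not isolate earliness. Adjustment deals only with measured entry day; it does not remove other selection by staff who knew their arm.

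**What to change.** 1. Derive days on sick leave at inclusion for every patient, from MiDAS or the baseline data. That MiDAS holds spell start dates is an assumption; the article says only that it registers sick leaves exceeding two weeks.
2. Report the distribution of entry day by arm.
3. Include entry day as a covariate in the primary comparison between arms, specified before outcome data are examined.
4. State whether the 60-day exclusion counts the current spell, so that the entry range is clear.
5. Word the conclusion as the effect of the whole procedure started at certificate renewal versus usual care. Label any contrast of arm by entry day as exploratory.

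The cost is one extra covariate and a few lines of text. Recruitment has closed, but the outcome analysis is described as still to come, so the change is feasible. If entry day proves balanced, adjustment does little harm and may add precision where entry day predicts outcome.
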